### Outcomes

For an overview of all outcomes and assessments, please see Table 1.

**Table 1 Tab1:**
[figure not shown]
Outcomes and time points for assessment in the trial. Specification of all outcome measures at each time point in the trial

Legend:

^a^Development and Well-being Assessment (DAWBA); ^b^Kiddie-Schedule for Affective Disorders and Schizophrenia (K-SADS); ^c^Reynolds Intellectual Assessment Scales (RIAS); ^d^Cambridge Automated Neurocognitive Test Battery (CANTAB); ^e^Rapid Visual Information Processing (RVP); ^f^Attention Attention Deficit Hyperactivity Disorder-Rating Scale (ADHD-RS); ^g^Behavior Rating Inventory of Executive Functions (BRIEF); ^h^Switching Task (AST); ^i^Match to Sample (MTS); ^j^Choice Reaction Time (CRT); ^k^Stop Signal Task (SST); ^l^Spatial Working Memory (SWM); ^m^Stockings of Cambridge (SOC); ^n^Intra-Extra Dimensional Set Shift (IED); ^o^Paired Associates Learning (PAL); ^p^Weis’s scale of disability-Parent Report (WFIRS-P)

Each CANTAB assessment lasts between 70 and 90 minutes and is collected between 8:30 am and 2:00 pm. While the child is assessed, questionnaire data from the parents are collected. If the child is unable to complete the assessment in one session, the assessment can be split up

Each CANTAB assessment lasts between 70 and 90 minutes. We aim to collect all cognitive assessments between 8:30 am and 2:00 pm to avoid a time of the day that would have an impact on the cognitive performance. While the child is being assessed, the parent questionnaire data are collected. If the child is unable to complete the assessment in one session, the assessment can be split up.

### Primary outcome

CANTAB is a nonverbal computerized cognitive test battery with solid psychometric properties [64–66] (Cambridge Cognition Limited, 2011). The primary outcome is the sustained attention test from the CANTAB: “Rapid Visual Information Processing (RVP) probability of hit,” assessed at the end of the intervention.

### Secondary outcomes

The following secondary outcomes will be assessed at the end of the intervention:Parent-rated ADHD symptoms assessed by ADHD-Rating Scale (ADHD-RS) (parent edition) [67].Teacher-rated ADHD symptoms assessed by ADHD-RS (teacher edition) [67].Parent-rated behavior assessed by Behavior Rating Inventory of Executive Functions (BRIEF) (parent edition) [68].Teacher-rated behavior assessed by BRIEF (teacher-edition) [68].

### Exploratory outcomes

The following exploratory outcomes will be assessed at the end of the intervention:CANTAB Attention Switching Task (AST).CANTAB Match to Sample (MTS).CANTAB Choice Reaction Time (CRT).CANTAB Stop Signal Task (SST).CANTAB Spatial Working Memory (SWM).CANTAB Stockings of Cambridge (SOC).CANTAB Intra-Extra Dimensional Set Shift (IED).CANTAB Paired Associates Learning (PAL).CANTAB RVP Probability of False Alarms.CANTAB RVP Reaction Latency S.D.BRIEF *(Inhibit)* (parent-rated).BRIEF *(Shift)* (parent-rated).BRIEF *(Emotional Control)* (parent-rated).BRIEF *(Initiate)* (parent-rated).BRIEF *(Working Memory)* (parent-rated).BRIEF *(Plan/Organize)* (parent-rated).BRIEF *(Organization of Materials)* (parent-rated).BRIEF *(Monitor)* (parent-rated).BRIEF *(Inhibit)* (teacher-rated).BRIEF *(Shift)* (teacher-rated).BRIEF *(Emotional Control)* (teacher-rated).BRIEF *(Initiate)* (teacher-rated).BRIEF *(Working Memory)* (teacher-rated).BRIEF *(Plan/Organize)* (teacher-rated).BRIEF *(Organization of Materials)* (teacher-rated).BRIEF *(Monitor)* (teacher-rated).Weis’s scale of disability-Parent Report (WFIRS-P) (Weis et al., 2005).Non-serious adverse events.Serious adverse events.

Further, all outcomes will be assessed again 12 and 24 weeks after the end of the intervention (Fig. 2).

**Fig. 2 Fig2:**
[figure not shown]
Timeline of the study enrollment. Timeline of participant assessments in the trial. 1) SDQ, Strength and Difficulties Questionnaire; 2) DAWBA, Development and Well-being Assessment; 3) K-SADS, Kiddie-Schedule for Affective Disorders and Schizophrenia; 4) RIAS, Reynolds Intellectual Assessment Scales; 5) CANTAB, Cambridge Automated Neurocognitive Test Battery; 6) ADHD-RS, Attention Deficit Hyperactivity Disorder-Rating Scale; 7) BRIEF, Behavior Rating Inventory of Executive Functions; 8) WFIRS-P, Weis’s scale of disability-Parent Report; and 9) TAU, treatment as usual

### Ethical issues

This trial is being conducted in accordance with the protocol approved by the Danish Data Protection Agency (ID.nr. 2008-58-0035) and the Regional Scientific Ethical Committees for Southern Denmark (nr. S20120096). The protocol is in accordance with the latest version of the Declaration of Helsinki. No significant deviation from the protocol will be implemented without prior review and approval by the regulatory authorities unless it may be necessary to eliminate an immediate hazard to the trial participants. In this case, the deviation will be reported to the regulatory authorities as quickly as possible.

A child can participate in the trial if the written consent of both parents is obtained. The patients’ treatment as usual will not be affected, including the use of medications, by their participation in this trial. When testing with CANTAB, patients will be asked to postpone any ADHD medication for 24 hours before testing, when medical treatment can affect efficacy measures. Trial participants will receive a gift certificate worth DKK 400 for participation. Transportation costs will be reimbursed.

The processing of personal data will be respected. There are no known risks associated with the use of computerized cognitive training. The method has been tested in many studies with patients with schizophrenia (see reviews [69, 70]) and in children with ADHD [38–40, 53]. No adverse events have been reported.

### Discontinuation and withdrawal

Although parents may have agreed to participate, they can always withdraw their child from the trial without further explanation. Pulling a child out of the trial, will not affects his or her further treatment. Patients can choose to stop at any time in the trial. Patients who were randomized will be included in the intention-to treat analyses unless they completely withdraw consent. In this case, all data regarding this participant will be deleted.

### Statistical plan and data analysis

#### Sample size

We are planning a trial of a continuous response variable, “CANTAB RVP probability of hit,” from an independent control, and experimental participants will be allocated at a 1:1 ratio. In a pilot project ([name] et al., unpublished data), adolescents with ADHD played a set of games from Scientific Brain Management for 7 weeks. Here, the “CANTAB RVP probability of hit” was normally distributed, with a standard deviation (SD) of 0.22 points. If the true difference in the experimental and control mean is 0.13 points, we will need to include 61 experimental participants and 61 control participants to be able to reject the null hypothesis that the population means of the experimental and control groups are equal with a probability (power) of 90 %. The type I error probability associated with this test of this null hypothesis is 5 %. We will thus include 122 participants in total.

#### Power

Assuming the minimal relevant difference is 0.5 SD for all the secondary outcomes and the significance level of the various tests of Hommel’s procedure is within the range of alpha = 0.05 and 0.05/4 = 0.0125 and the sample size is 122, the power of the individual tests will range between 59 % and 78 % (Table 2). A power of 78 % is judged to be reasonable, whereas a power of 59 % is insufficient.

**Table 2 Tab2:** Power estimations for the secondary outcome measures ADHD-RS and BRIEF

Outcome	Minimal relevant difference	SD^a^	Sample size	Power assuming an alpha of 1.25 %	Power assuming an alpha of 5 %
ADHD-RS^b^ (parents-assessed)	5 points	10 points	122	59 %	78 %
ADHD-RS (teacher-assessed)	5 points	10 points	122	59 %	78 %
BRIEF^c^ (parents-assessed)	0.25 points	0.5 points	122	59 %	78 %
BRIEF (teacher-assessed)	0.25 points	0.5 points	122	59 %	78 %

Legend:

^a^SD, standard deviation

^b^ADHD-RS, attention deficit hyperactivity disorder rating scale. Minimal relevant difference and SD calculated from a previous pilot project ([name] et al. unpublished data)

^c^BRIEF, Behavior Rating Inventory of Executive Functions. Minimal relevant difference and SD calculated from the BRIEF professional manual [68]

#### Multiplicity and significance

For all outcomes, we will present the test statistic and the corresponding *P* values for exploratory purposes.

The purpose of the analysis of the secondary outcomes is to make additional claims of treatment benefits in addition to those already established by the analysis of the primary outcome. Consequently, multiplicity adjustments are needed. Multiplicity adjustments generally require a strong control of the familywise error rate. With regard to this, a useful approach is the gatekeeping approach [71], which we will apply in this trial.

There is one primary and four secondary outcomes. Thus, the primary outcome will be the gatekeeper of the family of secondary outcomes. The sample size has been estimated using a risk of type I error (alpha) of 0.05. The primary outcome will consequently be analyzed and interpreted according to a two-sided significance level of *P* ≤ 0.05. Thus, if P of the test of the primary outcome is ≤ 0.05, the primary outcome is assessed as statistically significant. In this case, we will use Hommel’s procedure, which is uniformly more powerful than the Holm as well as the Hochberg adjustment procedures. This means that the alpha of 0.05 can be transferred to the secondary outcomes that will be tested in a pre-specified sequence at the 0.05 level of significance (see sequence in Table 2). The approach requires that as soon as the *P* value of a test is > 0.05, the null hypotheses of the remaining secondary outcomes are accepted regardless of the test statistics.

If *P* of the test of the primary outcome is > 0.05, the primary outcome is assessed as statistically insignificant. Consequently, the trial result is insignificant, and all the null hypotheses of the four secondary outcomes will be accepted regardless of the test statistic.

All exploratory outcomes and exploratory analyses of the primary and secondary outcomes will likewise be subject to statistical tests. However, if P of the test is ≤ 0.05, the outcome will not be assessed as statistically significant due to multiplicity and the increased risk of a type I error. Likewise, if P > 0.05, we cannot assess the outcome as statistically insignificant due to a potential lack of power. All exploratory analyses will thus be strictly hypothesis generating.

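### The rule for the four secondary outcomes names Hommel's procedure but then defines a fixed-sequence test; the two can license different claims from the same P values

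*Protocol article*

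**What the plan says.** The section Multiplicity and significance sets up a gate: "There is one primary and four secondary outcomes", and the secondaries are tested for claims only if the primary reaches two-sided P ≤ 0.05. For the secondary family it says "we will use Hommel’s procedure, which is uniformly more powerful than the Holm as well as the Hochberg adjustment procedures". The next sentence presents as a consequence of that choice that the outcomes are "tested in a pre-specified sequence at the 0.05 level of significance", with Table 2 supplying the order. As soon as one P value exceeds 0.05, "the null hypotheses of the remaining secondary outcomes are accepted regardless of the test statistics".

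Table 2 lists parent-rated ADHD-RS, teacher-rated ADHD-RS, parent-rated BRIEF and teacher-rated BRIEF. The Power section states that the significance level of the tests in Hommel's "procedure is within the range of alpha = 0.05 and 0.05/4 = 0.0125", and gives each outcome's power at both ends of that range: 59% and 78%.

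**The concern.** Hommel's procedure is a closed test built on Simes tests of the ordered P values. It takes no account of a pre-specified order, has no rule to stop at the first failure, and does not test every outcome at the full 0.05. A fixed sequence does all three. The second description therefore cannot be an explanation of the first.

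The Power section shows that this is more than a slip in one sentence. Under a fixed sequence every test is run at 0.05, so the 1.25% column and the 59% figure would have no role.

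At stake is which of the four secondary outcomes may be claimed. The section itself says that these analyses exist to add claims of benefit and that strong familywise control is therefore needed. That control has to be fixed in advance, and a text with two rules does not fix it.

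**Working it through.** **Inputs.** From the protocol: 61 per arm; 0.5 SD on each secondary (5/10 points for ADHD-RS, 0.25/0.5 for BRIEF); four secondary outcomes; alpha 0.05. Assumed: a common correlation rho between the four test statistics, because the protocol gives none. Results are shown for rho = 0, 0.5 and 0.8.

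**1. The plan's own figures.** The noncentrality is 0.5 × √(61/2) = 2.76. With 120 degrees of freedom, the noncentral t gives power of 78.2% at alpha 0.05 and 59.0% at 0.0125. Table 2 is reproduced, and it is a table of Hommel levels.

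**2. Same P values, two rules** (Table 2 order). Hommel rejects an outcome only if the Simes test rejects every subset of outcomes that contains it. For a subset of size k, Simes rejects if the j-th smallest P is at most 0.05 × j/k for some j.

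- *0.06, 0.004, 0.004, 0.004.* Sequence: the first P exceeds 0.05, so there are no claims. Hommel: 0.004 is below 0.05/4 = 0.0125, 0.05/3 = 0.0167, 0.05/2 = 0.025 and 0.05, so outcomes 2 to 4 are claimed (adjusted P 0.06, 0.008, 0.008, 0.008).
- *0.04, 0.3, 0.5, 0.6.* Sequence: outcome 1 is claimed and testing stops at outcome 2. Hommel: 0.04 > 0.0125, 0.3 > 0.025, 0.5 > 0.0375 and 0.6 > 0.05, so the test of all four together fails and nothing is claimed (adjusted P 0.16 for outcome 1).
- *All four P ≤ 0.05.* Both rules claim all four.

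The rules can part only when at least one P exceeds 0.05. Neither rule is always the stricter. These examples need no assumption about correlation.

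**3. How often they differ, and the error if the rule is chosen afterwards.** This was simulated with at least 200,000 trials per setting, normal test statistics, and the gate taken as open.

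| rho (assumed) | Claims differ, 0.5 SD on all four | Any false claim if either rule may be used, all four secondary nulls true |
|---|---|---|
| 0 | about 49% | about 8.5% |
| 0.5 | about 31% (separate runs 30% to 32%) | about 7.6% |
| 0.8 | about 18% | about 6.2% |

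Hand check of the last column at rho = 0: the sequence makes a false claim with probability 0.05. If the first P exceeds 0.05 (probability 0.95), Hommel can claim something only if the other three P values meet 0.0125, 0.025 or 0.0375 in order. That is a three-outcome Simes test at 0.0375, which has probability 0.0375. The ceiling is 0.05 + 0.95 × 0.0375 = 0.0856, in line with the simulation. Taken alone, each rule stayed at about 5% or below.

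**4. Power per outcome, gate open, 0.5 SD on all four.** Hommel gives about 72% to 73% for every outcome. The sequence gives about 79% for the first. At rho = 0 the fourth is 0.788⁴ = 0.386, or 39%; at rho = 0.5 simulation gives about 54%.

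**The case against.** The reach is limited, and that stands. The primary outcome, its alpha, the sample size and the gate are untouched. The question arises only if the primary succeeds and at least one secondary P exceeds 0.05. The section also promises test statistics and P values for all outcomes, so a reader could apply either rule.

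Three stronger readings are tempting, and the documents do not support them.

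- *That the plan as written has a familywise error of 8.5%.* Nothing says that the favourable rule will be picked. The figure needs that choice to be made after the data, an open gate and all four secondary nulls true. If the primary null is also true, the gate bounds any secondary claim at 5%.
- *That Hommel was clearly the intended rule.* The Power section and Table 2 point that way. But the operative sentences give an order, a level and a stopping rule. The Power section also judges 78% reasonable and 59% insufficient, which leans towards testing at 0.05. The text does not settle it.
- *That the rules give opposite findings.* They differ in which outcomes may be claimed, never in the direction of an effect.

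It could also be said that a separate analysis plan may settle the rule. It may, but this is not detail left out: the article states two incompatible rules as one, and a plan choosing either would contradict part of this text.

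**Conclusion.** The contradiction is real and stands in the current text. The two worked examples show it without assumptions. The frequency of differing claims, about 18% to 49%, depends on the assumed correlation, on 0.5 SD for all four outcomes and on an open gate. Four ratings of the same children may be strongly correlated, which would put the figure towards the lower end. The error of about 6.2% to 8.5% describes what an after-the-fact choice could do; it is not a property of either rule. What is lost as written is prior specification of the familywise control that the section says is needed.

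**What to change.** State one rule before unblinding, and preferably before the coded X/Y analysis is run, because two-sided P values are visible there whichever arm is which. Either route is sound:

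- **(a) Gatekeeper, then Hommel.** Keep the primary as gatekeeper, apply Hommel at familywise 0.05 across the four secondaries, and report adjusted P values. Delete the sentences on the sequence and on stopping. The Power section and Table 2 can stay as they are.
- **(b) Gatekeeper, then fixed sequence.** Keep the Table 2 order, 0.05 per test and the stopping rule. Remove Hommel from both sections, drop the 1.25% column of Table 2, and add cumulative power along the sequence.

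The cost is a few sentences, with no patients and no data. There is a genuine trade-off. With the gate open, route (a) gives up some power on parent-rated ADHD-RS (about 79% to 72%). Route (b) lowers teacher-rated BRIEF from about 72% to between 39% (rho 0) and 54% (rho 0.5). The sponsor should choose according to whether one outcome deserves priority.

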#### Analytical model

For the analysis of the continuous outcomes, structural equation models (for example, “proc calis” in SAS 9.3) including the direct maximum likelihood method (full information likelihood) will be used (see section on missing values). If the assumptions of a regression analysis are not fulfilled, a non-parametric test will be used (van Elteren’s test with stratification by one variable “center”). For dichotomous outcomes, we will use logistic regression to compare the results in the two groups.

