#### Missing values

In the analysis of the continuous variables, structural equation models (for example, “proc calis” in SAS 9.3) that include the direct maximum likelihood method (full information likelihood) will be used. Applying this method implies that unbiased estimates of the regression parameters will be obtained as long as the values are only missing at random. To improve the efficiency, all auxiliary variables present among the outcomes will be added to the model. An auxiliary variable is defined as a variable not in the analytical model but correlated (defined as |r| > 0.40) with one or more variables that 1) have missing values, and 2) are included in the analytical model. Thus, the auxiliary variables included may vary from one regression equation to the next one.

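### Maximum-likelihood tests at 122 children run slightly above the nominal 5 % (about 5.6 to 5.9 %) unless a small-sample correction is applied

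*Protocol article*

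**What the plan says.** Under Analytical model, continuous outcomes are analysed with structural equation models, "including the direct maximum likelihood method (full information likelihood) will be used"; the SAS procedure is given only as an example. The Missing values section repeats this choice and says that "all auxiliary variables present among the outcomes will be added to the model", an auxiliary being a variable that correlates above 0.40 in absolute value with an incomplete variable in the model. The Adjustments section adds centre, medication at baseline and the baseline value of the outcome.

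On the error rate, the Sample size section says "The type I error probability associated with this test of this null hypothesis is 5" %. Multiplicity and significance says "The sample size has been estimated using a risk of type I error (alpha) of 0.05" and that the primary outcome is "analyzed and interpreted according to a two-sided significance level of" P ≤ 0.05. The primary outcome is the gatekeeper for the four secondary outcomes.

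The article does not say whether P values come from a normal, t or likelihood-ratio reference. It mentions neither a small-sample correction nor its absence. If the regression assumptions fail, van Elteren's test replaces the model. If recruitment ends before 122, the Sequential analysis section plans a trial sequential analysis with a type I error of 5 %.

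**The concern.** Maximum likelihood estimates the residual variance with divisor N. That estimate is biased downward by the factor (N − k)/N, where k is the number of mean coefficients. In a large trial this is negligible. At 122 children with 6 coefficients it is small but not zero, and standard likelihood inference carries it into the standard errors, confidence intervals and P values.

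The gatekeeping scheme is meant to give strong control of the familywise error rate at 5 %, and it hangs on one primary test. If that test has a true size somewhat above 5 %, the gate opens slightly too often. The secondary tests share the same feature, and all the intervals are slightly too narrow.

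**Working it through.** **The plan's own figures.** Inputs from the Sample size section: "If the true difference in the experimental and control mean is 0.13 points"; the pilot outcome "with a standard deviation (SD) of 0.22 points"; "with a probability (power) of 90" %; two-sided alpha 5 %; 1:1 allocation.

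n per arm = 2 × (1.960 + 1.2816)² × 0.22² / 0.13² = 60.2, rounded up to 61, so 122 in total. Power at 61 per arm is 90.4 % by the normal formula and 89.9 % by the noncentral t. Table 2 also reproduces: by the noncentral t, 78.2 % at alpha 5 % and 59.0 % at 1.25 % (stated 78 % and 59 %). The sample size is not in question.

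**Number of coefficients.** Intercept 1, arm 1, centre 2 (three sites), medication 1, baseline value 1: k = 6. This count is mine, from the Adjustments and Randomization sections. At N = 122 the residual degrees of freedom are 122 − 6 = 116.

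**Bias in the standard error.** ML standard error / unbiased standard error = √((N − k)/N) = √(116/122) = 0.975, that is, about 2.5 % too small.

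**True size with complete normal data.** The ordinary regression t statistic follows t with N − k degrees of freedom exactly. Each likelihood-based rule rejects when |t| exceeds a threshold c, so the size is 2 × P(t on N − k df > c).

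- ML standard error, normal reference: c = 1.960 × √((N − k)/N)
- Likelihood-ratio test: c = √((N − k) × (exp(3.841/N) − 1))
- ML standard error, t reference: c = t(0.975; N − k) × √((N − k)/N)

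At N = 122:

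| Rule | c | True size |
|---|---|---|
| ML standard error, normal reference | 1.911 | 5.85 % |
| Likelihood ratio | 1.926 | 5.65 % |
| ML standard error, t reference | 1.931 | 5.6 % |
| Unbiased variance, normal reference | 1.960 | 5.2 % |
| Unbiased variance, t reference | 1.981 | 5.0 % |

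The first three rules use the uncorrected ML variance or likelihood, and all exceed 5 %. A nominal 95 % interval from them covers 94.1 to 94.4 %.

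**Fewer children, complete data.** These sizes apply only if P ≤ 0.05 remains the decision rule.

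| N | ML, normal | Likelihood ratio | ML, t |
|---|---|---|---|
| 100 | 6.0 % | 5.8 % | 5.7 % |
| 80 | 6.3 % | 6.0 % | 5.9 % |

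**Missing outcomes and auxiliaries.** The article gives no missing rate and no number of auxiliaries, so these settings are assumptions. Simulating the full-information estimator with a normal reference at N = 122 (40,000 runs per setting) gave 5.9 % with complete data. With 15 % of outcomes missing it gave 5.9 % with no auxiliaries, 5.9 % with 3 and 6.0 % with 6.

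**Power.** At a difference of 0.13 and SD 0.22, with no gain credited to the baseline covariate, power is 91.1 % with the ML standard error and a normal reference, and 89.9 % with the unbiased variance and a t reference.

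**The case against.** The strongest reply is that the article states nothing false. Full-information likelihood under missing at random is a legitimate choice. The reference distribution, variance divisor and degrees of freedom are details usually left to the full protocol or analysis plan, which is not shown and may correct for this. That stands, and it is why the point is conditional on no correction. What remains is that the chosen estimator produces the excess by default, whichever of the three likelihood-based references is used.

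Three stronger readings are tempting, and the document does not support them.

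- **That the plan uses large-sample z tests, so the true error simply is about 6 %.** No z test is stated. The supportable figure is a range of 5.6 to 5.9 % without correction.
- **That the error reaches 6.5 to 7.5 % if recruitment stops early.** With complete data and a normal reference this needs about 45 to 70 children, or roughly 55 to 85 with 15 % missing. The article gives no such number. It also plans a sequential analysis for that case. With an O'Brien-Fleming-type boundary (my assumption; none is stated), even the uncorrected normal-reference test would have size of about 1.0 % at 60, 2.3 % at 80 and 3.9 % at 100. The text does not make clear whether that analysis replaces or supplements the P ≤ 0.05 rule.
- **That adding auxiliaries necessarily makes it worse.** In 20,000-run simulations with 10 % missing, going from 0 to 10 auxiliaries moved the size from 5.87 to 6.14 % at N = 122, about 1.1 Monte Carlo standard errors, and from 6.74 to 6.62 % at N = 80. A marked rise appeared only in an extreme setting of 20 % missing and 20 auxiliaries (6.6 % at N = 122, 7.5 % at N = 80).

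The exact sizes also assume normal residuals. The fallback to van Elteren's test uses no ML variance and is not affected.

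**Conclusion.** The point holds in a limited form, as a minor one. With direct maximum likelihood, 6 mean coefficients and 122 children, uncorrected inference is mildly anti-conservative: 5.6 to 5.9 % against a nominal 5 %, an excess of 0.6 to 0.9 percentage points. This rests on complete, normally distributed data, on my count of coefficients, and on no small-sample correction being specified elsewhere. The excess grows modestly with fewer children if P ≤ 0.05 still decides. It does not affect the sample size or Table 2, and it does not show that the stated 5 % is wrong if the full plan already applies a correction.

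**What to change.** Keep the missing-at-random approach and the covariates, and add one sentence saying how P values and confidence intervals for the continuous outcomes are obtained. Any one of these would serve:

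- residual variance with divisor N − k and a t reference on N − k degrees of freedom, N being the children with an observed outcome. This is exact with complete normal data, and it returned 5.0 to 5.1 % in simulations with missing outcomes and no auxiliaries;
- an equivalent REML mixed model with Kenward-Roger degrees of freedom;
- multiple imputation followed by analysis of covariance, with Barnard-Rubin degrees of freedom.

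The last two suit the case where auxiliaries or other visits carry information on missing outcomes. Replacing the estimator or capping the auxiliary list is optional and not needed for this point. If the full analysis plan already has such a correction, a reference to it is enough.

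Cost: a change of wording, and about 1 percentage point of power (91.1 to 89.9 % in the calculation above), which leaves power at the planned 90 % to rounding.

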#### Adjustments

All analyses will be adjusted for the stratification variables (“center” and “pharmaceutical treatment at baseline”), and the outcome variable value will be assessed at baseline.

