#### Sensitivity analyses

Best-worst and worst-best sensitivity analyses of the primary outcome will be done. Here, missing values in one intervention group are imputed by the minimum value found in the total material (“best case”), and missing values in the other group are imputed by the maximum value found in the total material (“worst case”) and vice versa. The range of the estimates of the two regression parameters of the intervention indicator will convey an impression of the bias one may expect if values are missing not at random.

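### The non-parametric fallback stratifies by centre only, against the rule that all analyses adjust for centre and medication, and it leaves out the baseline value and the planned missing-data method

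*Protocol article*

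**What the plan says.** All places are in the protocol article, under Statistical plan and data analysis unless noted.

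- **Analytical model.** Continuous outcomes go into a structural equation model fitted by full-information maximum likelihood. Then: "If the assumptions of a regression analysis are not fulfilled, a non-parametric test will be used". The test named is van Elteren's, stratified by a single variable, centre.
- **Adjustments.** "All analyses will be adjusted for the stratification variables", which are listed as centre and drug treatment at baseline. The rest of the sentence, read literally, says only that the outcome is measured at baseline. Under that heading it very probably means that analyses are adjusted for the baseline value.
- **Missing values.** Continuous variables are analysed by full-information likelihood with auxiliary variables, on the ground that "unbiased estimates of the regression parameters will be obtained as long as the values are only missing at random". No exception is made for the fallback.
- **Randomization** (Methods/Design). Allocation is stratified by three sites and by medication, yes or no.
- **Primary outcome** (Methods/Design) and **Sample size.** The outcome is "Rapid Visual Information Processing (RVP) probability of hit". In the pilot it "was normally distributed, with a standard deviation (SD) of 0.22 points".

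**The concern.** The fallback and the adjustment rule cannot both be followed. A test stratified by centre alone drops one of the two randomisation factors and makes no use of the baseline RVP score, which every child is asked to provide. It also has no likelihood through which a child with a missing outcome could contribute.

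The trigger is plausible. The primary outcome is a probability, bounded at 0 and 1. Normality was seen in a pilot of adolescents who used a different set of games, whereas this trial enrols children aged 6 to 13. The primary test is also the gatekeeper for the four secondary outcomes (Multiplicity and significance), so the way it is done decides whether any confirmatory claim can be made.

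**Working it through.** **1. The passages side by side.**

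| | Adjustments / Missing values | Fallback |
|---|---|---|
| Centre | yes | yes (stratum) |
| Medication at baseline | yes, explicit | no |
| Baseline outcome value | yes, on the probable reading | no |
| Missing outcomes | full-information likelihood with auxiliary variables | none stated; the likelihood cannot be used |

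The medication conflict is explicit. The baseline conflict rests on the probable meaning of the garbled clause. On missing outcomes, the likelihood model allows missingness to depend on observed baseline, medication and auxiliary variables. A rank test on observed cases needs missingness to be unrelated to the outcome once arm and centre are known, which is the stronger assumption.

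**2. The plan's own figure.** The inputs are "If the true difference in the experimental and control mean is 0.13 points", SD 0.22, two-sided 5% and 90% power, giving "we will need to include 61 experimental participants and 61 control participants".

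- d = 0.13/0.22 = 0.591.
- n per arm = 2(1.960 + 1.282)²/0.591² = 60.2, rounded up to 61.
- Power at 61 = Φ(0.591 × √(61/2) − 1.960) = Φ(1.303) = 90.4%; the noncentral t gives 89.9%.

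The stated figure reproduces. It comes from an unadjusted comparison of two means and takes no credit for baseline.

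**3. Fallback and adjusted model under normality, complete data.** The rank test has efficiency 3/π = 0.955, so the effective n is 61 × 0.955 = 58.3 and power is Φ(0.591 × √(58.3/2) − 1.960) = 89.05%. The adjusted model replaces d by d/√(1 − r²). The correlation r between baseline and outcome is not in the document, so a range is assumed.

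| Assumed r | Adjusted model | Fallback | Gap (points) |
|---|---|---|---|
| 0 | 90.38% | 89.05% | 1.3 |
| 0.3 | 92.80% | 89.05% | 3.8 |
| 0.5 | 96.47% | 89.05% | 7.4 |
| 0.7 | 99.55% | 89.05% | 10.5 |

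The noncentral t gives 92.4%, 96.2% and 99.5% against 88.6% for r = 0.3, 0.5 and 0.7: gaps of 3.8, 7.6 and 10.9.

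**4. Simulation where assumptions may fail.** Van Elteren by centre was compared with a linear model on centre and baseline (plus medication in most normal runs and in the bounded runs), 61 per arm, r from 0 to 0.7, 2,000 to 3,000 runs per scenario. The Monte Carlo standard error near 88% is √(0.88 × 0.12/3000) = 0.6 points, or 0.7 with 2,000 runs.

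| Data | Fallback | Adjusted model |
|---|---|---|
| Normal | 87–89% | 89–99.6% |
| Bounded at 0 and 1 | 87–89% | 88–99% |
| Heavy tails (t, 3 df) | 97–99% | 89–98% |
| Strong skew (reversed log-normal) | about 100% | 89–98% |
| Normal, 10% of outcomes missing, observed cases in both | 82–85% | 84–99% |

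With complete heavy-tailed or skewed data the fallback lost in one scenario only (heavy tails, r = 0.7: 97.0% against 98.0%). The bounded runs assume a control mean of 0.6 before truncation. That puts about 3% of control scores (0.40/0.22 = 1.82 SD) and 11% of intervention scores (0.27/0.22 = 1.23 SD) at the ceiling, so they represent moderate bounding only.

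**5. Where the gap comes from.** With no medication effect, van Elteren had 87.0–88.1% power by centre and 86.4–87.5% by the six site-by-medication cells. With an assumed medication difference of 0.5 SD the figures were 87.5–88.9% and 87.6–90.0%. The gap in power therefore comes from the baseline value. Leaving out medication matters mainly because it contradicts the plan and the randomisation.

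**The case against.** A reader might infer that the fallback undercuts the planned power. The document does not support that. The 90% never relied on baseline, so the loss against it is 1 to 3 points with complete normal or bounded data. The larger gaps are measured against a model for which the trial was not powered, at correlations that the document does not give. The fallback is used only when assumptions fail, and under heavy tails or strong skew it usually has the higher power. This objection stands, and the power claim has to stay conditional. Nor should a larger contrast be built on a smaller trial: Sequential analysis says that recruitment may stop short of 122 but gives no number.

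A reader might also infer that the test could be picked to suit the result. The fallback is named in advance, and Blinding has the groups coded X and Y with both conclusions drawn before the code is broken. That limits steering in a chosen direction, although it does not stop an analyst from seeing both P values before settling on a test.

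A third inference is that the sensitivity and subgroup analyses collapse, since a rank test does not supply "The range of the estimates of the two regression parameters of the intervention indicator" or an interaction term. Nothing says that those analyses must follow the fallback, and the subgroup analysis is declared exploratory.

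Finally, the article never says that the fallback is an observed-case analysis, and a fuller plan may settle how missing outcomes enter it. That is fair. What remains is that Missing values is written for all continuous variables, and the named fallback cannot comply with it. None of this removes the conflict over medication.

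**Conclusion.** The point holds as an inconsistency in a contingent analysis of the primary outcome, and it should be corrected. It is explicit for the medication stratum, probable for the baseline value because of the garbled clause, and an unaddressed conflict for missing data.

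Its cost in power is small against the stated 90%: about 1 to 3 points with complete normal or moderately bounded data. It is about 4, 7 and 10 points against the baseline-adjusted model at assumed correlations of 0.3, 0.5 and 0.7, and similar for bounded scores. It can turn into a gain under heavy tails or strong skew. If outcomes are missing and the test uses observed cases, power falls further: 85.7% by formula and 82–85% simulated at an assumed 10% missing under normality. The case for change therefore rests on consistency with the adjustment rule, the randomisation and the missing-data method, not on a shortfall in planned power.

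**What to change.** Reconcile Analytical model, Adjustments and Missing values by replacing the fallback with one that keeps site, medication and baseline. Either of these would do:

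- robust (sandwich) or bootstrap standard errors for the pre-specified full-information model, which leaves the estimand, covariates and missing-data method unchanged; or
- a rank ANCOVA on the ranked baseline, stratified by site and medication, with stated handling of missing outcomes, for example multiple imputation. The six cells average 122/6 ≈ 20 children, so some may be sparse.

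State that assumptions are judged on residuals pooled over arms, before the coded X/Y comparison is seen. Report the adjusted mean difference with its confidence interval whichever test is used. Reword the Adjustments sentence to say that analyses are adjusted for the baseline value of the outcome.

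The cost is plan wording and a few lines of code, with no new data. Trial status gives recruitment as ongoing, so the change could be made before any group comparison is seen.
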